### Measures of bias

Measures of bias will include:Expectations about treatment: Prior to randomisation, older people with TR-GAD will be asked to rate how much they expect their symptoms to improve and how much they expect their life to improve if they receive ACT on a 5-point Likert scale from 0 (not at all) to 4 (completely). Therapists will be asked to rate the same questions after a participant's first therapy session;Treatment preferences: Prior to randomisation, older people with TR-GAD will be asked to rate how much they would hope to receive ACT plus UC and how much they would hope to receive UC alone on a 5-point scale from 0 (not at all) to 4 (completely);Contamination in the control arm: Receipt of other forms of psychological and pharmacological treatment for GAD outside of the trial will be recorded using the modified CSRI. Additional exploratory data analysis will be undertaken if reported by a substantial proportion of participants;*A*ssessment of blindness of outcome assessors: Outcome assessors will be asked to declare if they have been unblinded (and how) at 6- and 12-months follow-up. Those who have not been unblinded will be asked to guess whether they think participants were allocated to the intervention or control arm.

### Treatment fidelity

Treatment fidelity will be assessed in four areas:Training: Training workshops will be videoed and an independent ACT therapist will assess the fidelity of training to the ACT model. Therapists' knowledge of ACT will be assessed through their responses to a clinical vignette-based exercise at the end of training;Treatment delivery: All therapy sessions will be audio-recorded using an encrypted digital voice recorder, and 10% of randomly selected sessions will be rated on an ongoing basis throughout intervention delivery by an independent, experienced ACT therapist using the ACT Fidelity Measure [34]. The ACT-FM is a 25-item measure, which assesses ACT fidelity in 4 domains (open response style, aware response style, engaged response style and therapist stance). Scores for each subscale are summed in order to produce a total ACT consistency score and a total ACT inconsistency score. In addition, adherence to the treatment manual and therapy components will be measured using a checklist that therapists complete at the end of each session, which will be adapted from previous work [19];Treatment receipt: The Comprehensive Assessment of ACT processes [28] will be used to measure changes in psychological flexibility in older people with TR-GAD. Engagement with therapy will be defined by the number of sessions out of 14 attended: poor (0–3), moderate (4–6), good (7–10), excellent (11–14);Treatment enactment: An idiographic patient-reported outcome measure, the Goal-Based Outcomes tool [32], will be used to assess personally meaningful behavioural changes.

### Participant timeline

As shown in Fig. 1, older people with TR-GAD will be involved in the RCT for approximately 12 months (± 6 weeks) after randomisation.

**Fig. 1 Fig1:**
[figure not shown]
Timeline for older people with TR-GAD in the trial Notes: C-SSR = Columbia-Suicide Severity Rating Scale Screener, CALYs = Capability-adjusted life years, CIRS-G = Cumulative Illness Rating Scale-Geriatrics, CLAS = Cognitive & Leisure Activity Scale, CompACT = Comprehensive Assessment of ACT processes, CSQ-8 = Client Satisfaction Questionnaire-8, CSRI = Client Service Receipt Inventory, EQ-5D-5L = EuroQol-5 domains-5 levels, EQ-VAS = EuroQol visual analogue scale, G-BO = Goal-Based Outcomes tool, GAD-7 = Generalised Anxiety Disorder Assessment-7, GDS-15 = Geriatric Depression Scale-15, ICECAP-O = ICEpop capability measure for older people, IPDS = Iowa Personality Disorder Screen, MINI = Mini-International Neuropsychiatric Interview, MQOL-R = McGill Quality of Life Questionnaire-Revised, QALYs = Quality-adjusted life years, SMMSE = Standardised Mini-Mental State Examination

### Sample size

296 older people with TR-GAD (148 per arm) will be recruited from approximately 15 sites (11 in the UK and 4 in Australia). This will allow detection of an effect size of 0.37 standard deviations (SD), with a two-sided alpha of 5% and 90% power. This assumes: a) a correlation of 0.55 between scores at 0- and 6-months, as seen in our previous feasibility study [19]; b) 20% attrition at 6-months [19]; and c) an intraclass correlation coefficient of 5% among 30 therapists (two per site) in the intervention arm, similar to previous studies [35]. In order to maintain a 1:1 allocation per arm, the sample size will be modified to 148 participants per arm, which is sufficient to maintain 90% power.

Our effect size of 0.37 SD is based on the fact that: a) improvements of 3–4 GAD-7 units are regarded as clinically important changes to individual patients [36–39]; and b) a change of approximately 2 GAD-7 units (0.4 SD) would mean an additional 15% of people having a clinically important improvement of 3 units compared with UC, based on Normal distributional theory. This is similar to the 0.40–0.46 SD difference observed in systematic reviews of ACT for mental and physical health conditions and CBT for GAD [40–42]. Our effect size has been reduced from 0.4 to 0.37 SD in order to compensate for the inclusion of people with limited or no spoken English necessitating the use of an interpreter, which may affect engagement with ACT.

### Recruitment

#### Older people with TR-GAD

Potentially eligible participants will be identified and approached about the trial through one of four routes: a) local clinicians or clinical team administrators from GP surgeries, NHS Talking Therapies services and Community Mental Health Teams (or their equivalent in Australia); b) searches of GP electronic medical records (or their equivalent in Australia) and postal invitations to identified potentially eligible participants; c) self-referral through community and online advertisements; and d) clinical databases (in which people have already given consent for research contact) and research databases (including Join Dementia Research and the NIHR Be Part of Research Volunteer Service in the UK).

Many older people who meet diagnostic criteria for GAD are referred to primary and secondary care services with a diagnosis of major depression and comorbid anxiety or mixed anxiety and depression rather than GAD. Consequently, clinicians in the services noted above or a member of the local or central research team will pre-screen potential participants who are referred with these diagnoses (rather than GAD) using the Generalized Anxiety Disorder-2 (GAD-2), if they provide verbal consent to this. The GAD-2 is a 2-item questionnaire used to identify GAD in primary care [43]. If a potential participant scores ≥ 2 points on this scale [44], they will be asked to complete the Patient Health Questionnaire-2 (PHQ-2). This is a 2-item questionnaire used to identify depression in primary care [45]. If the PHQ-2 total score is higher than the GAD-2 total score then they will be asked whether the symptoms of depression or GAD are most distressing, severe or of most concern to them. If symptoms of GAD are most distressing, severe or of most concern to them, or if symptoms of GAD and depression are equally problematic, then the study will be further discussed with them.

Once potentially eligible participants have been identified and verbal consent for contact has been obtained, a member of the local or central research team will discuss the trial with them, either in person or via video call, telephone or email. If they express an interest in participating in the trial, they will be asked to verbally consent to completing the GAD-2 screening questionnaire, if not already completed. If they score ≥ 2 points on the GAD-2 and they continue to express an interest in participating in the trial then they will be given a Participant Information Sheet. If they are still interested in participating in the trial, the member of the local or central research team will arrange a screening appointment, either in person or via telephone or video call. During this appointment, fully informed written consent, audio-recorded verbal consent (via telephone or video call) or digital consent (via email or Qualtrics) to take part in the trial will be sought. Following this, eligibility for inclusion in the study will be determined through a screening interview.

Those who speak English as a second language or who speak no English necessitating the use of an interpreter will not be excluded. However, they will complete study procedures and outcome measures through interpreters, where necessary. Participant-facing documents such as the Participant Information Sheet, consent form, recruitment leaflet and recruitment poster will be translated into languages other than English where possible.

#### Trial therapists

Participants will be recruited from the group of trial therapists who will be involved in delivering the intervention to older people with TR-GAD. They will be approached about completing a qualitative satisfaction questionnaire by a member of the central research team. Other procedures will be similar to those described above.

### Randomisation

Eligible participants with TR-GAD will be randomised in a 1:1 ratio to one of two arms (ACT plus UC or UC alone) using a web-based, centralised randomisation system hosted by the Sheffield Clinical Trials Research Unit (SCTRU). Randomisation will be stratified by recruitment site. The concealed allocation sequence will be hosted by the SCTRU in accordance with their standard operating procedures (SOPs) and will be held on a secure server. Access to the concealed allocation sequence will be restricted to those with authorisation. A SCTRU statistician will set up the randomisation system, but neither statistician nor other trial team members will be able to view the randomisation list during the trial. Eligible participants will be randomised once fully informed consent has been provided and baseline measures have been collected.

### Blinding

At least one trial statistician will be blinded to allocation during the trial. It is intended that the outcome assessor will be blind to treatment allocation for the duration of the trial, while older people with TR-GAD, trial therapists and clinicians will be aware of this. Only the Data Monitoring and Ethics Committee (DMEC) will have access to unblinded data at their request during the trial. Any instances of accidental unblinding will be recorded at 6- and 12-months follow-up.

### Data collection

Fully informed consent will be obtained from all participants prior to any data collection. For older people with TR-GAD, data pertaining to socio-demographic and clinical characteristics will be collected at screening and baseline (see Fig. 1). Data collection will be conducted in person (at home or in clinic) or via video call, telephone, online via Qualtrics or post at 0 months, 6 months post-randomisation (± 6 weeks) and 12 months post-randomisation (± 6 weeks) by a blind outcome assessor. Table 3 lists exceptions to this. Mode of administration will be recorded at each time point. Numerous strategies will be used to promote participant retention, including the provision of non-contingent vouchers for completion of outcome measures at follow-up.

**Table 3 Tab3:**
[figure not shown]
Schedule of enrolment, interventions and assessments

*ACT* Acceptance and Commitment Therapy, *PR* post-randomisation, *UC* usual care

^a^As the modified CSRI includes a question about psychological therapies received, this will be administered in one of four ways at follow-up to prevent potential unblinding of outcome assessors: i) returned via post to the central study team; ii) via online methods; iii) by telephone by the non-blind outcome assessor arranging the follow-up visit, with the rest of the assessment being completed by the blinded outcome assessor; or iv) at the end of the outcome assessment session at 12 months, after the outcome assessor has completed the unblinding question

^b^After each session

^c^Serious adverse events can be reported at any time

^d^Completed after consent, but prior to randomisation, after participants are given a rationale for ACT

^e^Completed at the end of involvement in the trial

^f^Assessed on an ongoing basis throughout intervention delivery in 10% of randomly selected sessions

All older people with TR-GAD will be invited to complete an anonymous qualitative satisfaction questionnaire at 6-month follow-up via post, email or online via Qualtrics (or verbally via telephone, video call or face-to-face interview if necessary). Any questionnaires completed verbally will be conducted by an independent member of the local or central research team to avoid unblinding of outcome assessors. There will also be separate versions of the questionnaire for the intervention arm and UC arm to avoid unblinding of outcome assessors. Those in the intervention arm will be asked questions in relation to the acceptability of ACT and its suitability and relevance to older people with TR-GAD, perceived benefits and limitations of the intervention, perceived mechanisms of impact, facilitators of and barriers to implementing the intervention in their everyday lives, and recommendations for revising the intervention. Those in the UC arm will be asked questions in relation to the psychological aspects of their usual care. Questions will focus on what kind of formal and informal psychological support they received (if any), what was helpful and what was not, and what they felt would have been helpful.

All trial therapists will also be invited to complete an anonymous qualitative satisfaction questionnaire at the end of delivering ACT in the trial. This will collect brief data on socio-demographic and professional characteristics. It will then ask a combination of closed and open questions in relation to how ACT was delivered in practice, facilitators of and barriers to implementing the intervention in the NHS, and recommendations for revising the intervention.

### Data management

Study-specific procedures for data management will be detailed in a data management plan. Data collection, management and analysis will be overseen by SCTRU, who will ensure that the trial is undertaken according to SCTRU SOPs and Good Clinical Practice guidelines. Data will be collected and retained in accordance with the UK's Data Protection Act (2018), which complies with the Australian Privacy Principles (APP) set out in the Australian Privacy Act (1988).

Participants will be assigned unique identification codes, which will be used in all data storage and will not contain any names or other personally identifiable information. Case report forms will not bear the participant’s name or other personal identifiable data. Any personally identifiable information (such as contact details) will be stored in locked cabinets. No identifiable Australian patient data will be shared with the UK team. Confidentiality will be kept unless there is evidence of risk of harm to self or others.

Qualtrics will be used as a digital option to collect informed consent and trial data. Qualtrics has obtained ISO 27001, ISO/IEC 27017, ISO/IEC 27018 and ISO 9001 security certifications, which are internationally recognised, best practice frameworks for information security management systems. The SCTRU’s web-based data management system, Prospect, will be used to store trial data in a PostgreSQL database on virtual servers hosted by Corporate Information and Computing Services at the University of Sheffield. Prospect uses industry standard techniques to provide data security, including password authentication and encryption using Secure Sockets Layer/Transport Layer Security. Australian participants will be asked to consent to their personal and research data being transferred to and stored by the University of Sheffield within Prospect.

Verbal consent for trial participation, audio content of therapy sessions and verbal responses to qualitative satisfaction questionnaires (for those unable to complete a written version of this) will be audio recorded using encrypted digital voice recorders or Microsoft Teams recording functionality. Audio files will be uploaded to a secure server using University College London’s Data Safe Haven, which satisfies the highest level of security requirements of NHS trusts. They will then be transferred and stored on UCL’s password protected secure electronic network. Australian participants will be asked to consent to their audio files being transferred to and stored by University College London’s Data Safe Haven.

In line with the sponsor’s data protection policy, UK study documentation and pseudonymised data will be securely kept for a period of 10 years following completion of the study. Australian study documentation and pseudonymised data stored in Australia will be securely kept for a period of 15 years following completion of the study.

### Statistical methods

A statistical analysis plan will be developed, reviewed and approved by the Trial Steering Committee (TSC) prior to data analysis. The primary outcome will be analysed using multi-level modelling, which will include fixed effect covariates (treatment arm and baseline score) and a random effect covariate (therapist) to account for potential clustering. Separate analyses will be conducted at 6-months (primary analysis timepoint) and 12-months follow-up. The difference between treatment arms in mean GAD-7 total score and its 95% confidence interval will be quantified by the model coefficient. Primary analyses will be by intention to treat, but additional sensitivity analyses will assess the impact of session uptake using complier-average causal effect (CACE) analyses to model the average treatment effect among those who were considered “compliant” with ACT. For the purpose of trial data analysis, completion of seven sessions will be regarded as a minimum number allowable for an adequate exposure to treatment in the protocol, with participants that receive fewer than seven sessions being a deviation from this. As the minimum dose can vary across participants, this will be assessed further using a CACE analysis in which treatment outcome will be examined in relation to the number of sessions received. In addition, sensitivity analyses will examine the consistency of outcomes across sites, baseline GAD severity, age at first onset and baseline psychotropic medication use.

Secondary outcomes will be analysed in a similar manner to the primary outcome. Additional exploratory analyses will be undertaken to assess the consistency of treatment effects across a variety of subgroups. These will include treatment preference and expectations, psychiatric comorbidity, limited or no spoken English skills, country of recruitment and mode of therapy delivery. The impact of contamination (e.g. psychological therapy in the control arm) will be assessed in a per-protocol analysis [46].

It is expected that there will be missing outcome data for some participants, either due to study withdrawal, loss to follow up or death. The number of missing values will be summarised by treatment arm, time point and reason. Multiple imputation using Rubin's rules [47] will be implemented for the primary endpoint. Adverse events will be summarised in terms of the number and percentage of participants experiencing each event and the number of events by treatment arm.

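### Randomisation is stratified by recruitment site, but the listed primary model has no site term; if sites differ, the test is somewhat conservative

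*Protocol article*

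**What the plan says.** The Randomisation section of the protocol article states: "Randomisation will be stratified by recruitment site". It names no other factor.

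The Statistical methods section specifies the primary analysis as a multi-level model "which will include fixed effect covariates (treatment arm and baseline score) and a random effect covariate (therapist) to account for potential clustering". Secondary outcomes are to be handled similarly. Site is mentioned in that section only where it says that "sensitivity analyses will examine the consistency of outcomes across sites".

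The Sample size section says that "296 older people with TR-GAD (148 per arm) will be recruited from approximately 15 sites". Its clustering allowance is "an intraclass correlation coefficient of 5% among 30 therapists (two per site) in the intervention arm". It has no term for site.

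**The concern.** Stratifying by site balances the arms within each site, so differences in level between sites largely cancel from the treatment contrast. A model without site does not know this and leaves that variation in the standard error.

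The therapist effect does not stand in for site. Therapists are nested in sites and cluster only the ACT arm. Site variation in ACT is therefore absorbed as extra therapist variance, and in usual care it falls into the residual. The planned look at consistency across sites is a check on heterogeneity and leaves the primary standard error as it was.

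Some between-site variation is plausible. The Comparator section itself expects usual care to vary by site, and the roughly 15 sites span two countries and several kinds of service. At stake is a primary confidence interval somewhat wider than the design warrants, with the same feature passed on to the secondary outcomes.

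**Working it through.** **Inputs from the Sample size section.** 148 per arm; "an effect size of 0.37 standard deviations (SD), with a two-sided alpha of 5% and 90% power"; "a correlation of 0.55 between scores at 0- and 6-months"; "20% attrition at 6-months"; therapist intraclass correlation 0.05 with 30 therapists, ACT arm only.

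**Assumed input.** The share ρ of residual variance (after baseline adjustment) that lies between sites. The article does not give it, so I use 0, 0.02, 0.05 and 0.10.

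**Step 1: the plan's own figure.** Residual variance after baseline adjustment is v = 1 − 0.55² = 0.6975 (SD units). Without clustering, n per arm = 2(1.96 + 1.2816)² × 0.6975 / 0.37² = 107.1, so 108, and 108/0.8 = 135 after attrition. With 148 per arm, 148 × 0.8 = 118.4 are analysed, or 118.4/30 = 3.95 per ACT therapist. The ACT design effect is 1 + 2.95 × 0.05 = 1.147.

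- SE = √[0.6975 × (1.147/118.4 + 1/118.4)] = 0.1125
- Power = Φ(0.37/0.1125 − 1.96) = 90.8%

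Taking therapist caseload before attrition (148/30 = 4.93) gives 90.2%. The total needed for 90% power is 288 or 294 under these two conventions, so the stated 296 reproduces.

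**Step 2: standard errors with site variation.** With exact balance within sites, site cancels from the contrast and the true variance is

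V_true = v × [(1 − ρ − 0.05)/118.4 + 0.05/30 + (1 − ρ)/118.4].

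Without a site term, site variance joins the therapist variance in ACT and the residual in usual care, so the model reports

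V_model = v × [(1 − ρ − 0.05)/118.4 + (0.05 + ρ)/30 + 1/118.4].

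For ρ = 0.05:
- V_true = 0.6975 × (0.007601 + 0.001667 + 0.008024) = 0.01206, SE 0.1098
- V_model = 0.6975 × (0.007601 + 0.003333 + 0.008446) = 0.01352, SE 0.1163
- Ratio 1.059

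**Step 3: test size and power.** Type I error as written is 2[1 − Φ(1.96 × SE_model/SE_true)]. Power as written is Φ[(0.37 − 1.96 × SE_model)/SE_true]. With site it is Φ(0.37/SE_true − 1.96).

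| Site share ρ (assumed) | SE without site | SE with site | Overstatement | Type I error as written | Power as written | Power with site |
|---|---|---|---|---|---|---|
| 0 | 0.1125 | 0.1125 | 0% | 5.0% | 90.8% | 90.8% |
| 0.02 | 0.1140 | 0.1114 | 2% | 4.5% | 90.6% | 91.3% |
| 0.05 | 0.1163 | 0.1098 | 6% | 3.8% | 90.2% | 92.1% |
| 0.10 | 0.1199 | 0.1071 | 12% | 2.8% | 89.6% | 93.2% |

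**Step 4: simulation check.** REML fits to simulated trials (15 sites, two therapists per site, 236 completers, 600 replicates per setting) compared the model without site with one adding site indicators. At an effect of 0.37 SD, the mean model SE was:
- ρ = 0.02: 0.1135 against 0.1122 (1.2% larger)
- ρ = 0.05: 0.1154 against 0.1109 (4.1% larger)
- ρ = 0.10: 0.1181 against 0.1085 (8.8% larger)

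The spread of the estimates was practically the same under both models, so the difference lies in the reported SE. Power without and with site was 91.5% and 92.2%, 87.2% and 89.8%, and 89.8% and 93.7%. In the null runs, rejection rates without and with site were 0.053 and 0.053, 0.033 and 0.050, and 0.028 and 0.048. A random site intercept gave nearly the same results as site indicators.

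Monte Carlo error is about 1.2 points for power and 0.9 points for type I error. The null run with no site variance gave 0.033 and 0.032, so no single rejection rate should be pressed. The paired comparison of SEs is the firmer evidence. It supports the direction, with smaller differences than the closed form.

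**The case against.** **The statistical analysis plan may add site.** The article promises such a plan, approved before analysis, and saying what the model will include does not expressly rule out a further term. This stands in part: site could be added there without contradicting the article. But the article does list its fixed and random terms, and the one stratification factor is not among them. That is a specification to correct, beyond a detail left open.

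**The effect is conditional and unquantified.** This stands in full. Only site variation left after adjusting for baseline GAD-7 matters, no site correlation is given, and nothing in the article supports a share as high as 0.10. With no site variance there is nothing to gain.

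**The closed form exaggerates.** It assumes exact balance within sites, which 20% attrition disturbs, and the simulated differences are smaller. This stands, and is why the percentages are an upper guide.

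**A stronger reading is tempting.** A reader might infer that the trial is underpowered, that its estimate is biased or that its false-positive rate is inflated. None of this follows. The error is conservative and the estimate is not biased. In the closed form, power as written stays between 89.6% and 90.8%, about the planned 90%. What is lost is precision relative to a site-adjusted model.

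**Conclusion.** The point holds as a low-severity improvement. The listed primary model does not reflect the stratified randomisation, and neither the therapist effect nor the consistency check repairs that. If sites differ after baseline adjustment, the reported standard error is too large: at most about 2% to 12% for assumed site shares of 0.02 to 0.10. The cost, relative to a model with site, is about 1 to 4 power points (0.7, 1.9 and 3.6 in the unrounded closed form).

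These sizes rest on the plan's own correlation, attrition and therapist clustering, on the assumed site shares, and on near balance within sites. The omission itself is certain from the text; its size is not. It is not a defect that must be repaired before the trial can give a valid answer.

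**What to change.** Add recruitment site to the primary model, either as a random intercept with ACT therapists nested within site or as site indicators. A random intercept uses few degrees of freedom if some sites stay small. Carry the same term into the secondary-outcome models and the multiple-imputation model.

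The cost is one line in the Statistical methods section and the statistical analysis plan, with no new data and no change to the 296 participants. It should be settled before any outcome data are analysed, because a site term added afterwards would look post hoc.

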### Outcomes

The primary outcome measure will be the Generalised Anxiety Disorder Assessment-7 (GAD-7) [25]. This is a 7-item self-report measure of GAD, which is routinely used with adults of all ages within primary and secondary care in the NHS. The GAD-7 will be completed at baseline (0 months), following confirmation of eligibility and consent, 6 months post-randomisation (the primary endpoint), and 12 months post-randomisation.

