### Economic evaluation

A health economic analysis plan will be developed, reviewed and approved by the TSC prior to data analysis. A within-trial cost-utility analysis will present the incremental costs per quality-adjusted life year gained of older people with TR-GAD receiving tailored ACT plus UC compared to UC alone from an NHS and social care perspective. Costs will be estimated on a per-participant basis and will include costs for delivering the intervention. The modified CSRI will be used to collect data on health and social care resource use. Unit costs will be derived from relevant national sources and will include NHS reference costs and Personal Social Service Research Unit costs [48]. The standard version of the EQ-5D-5L will be used to collect patient reported health status. Values for EQ-5D-5L for England will be used based on NICE advice at the time of analysis, which may either be to use the value set currently in collection or a mapping approach. These will be calculated using the area under the curve method. Appropriate multiple imputation techniques will be implemented where data on the EQ-5D-5L or resource use are missing. Differences in costs and quality-adjusted life years between the treatment arms will be described and the incremental cost effectiveness ratio, with associated uncertainty, will be calculated.

Clinical effectiveness data will be used to judge whether there is evidence of continued benefit from the treatment at 12 months and any evidence of a waning of effect. This will determine if there are grounds to extrapolate the analysis beyond the 12 months observed period using a simple decision model to estimate costs and benefits. This may be important since continued health benefits are unlikely to be matched by increased costs, given the upfront costs of providing the intervention. The time period for the model or appropriate methods for extrapolation cannot be determined at this stage. Any model based extrapolation will adhere to standard methods to reflect uncertainty including probabilistic sensitivity analysis and one-way/multi-way analyses. A separate analysis of over-the-counter medication will also be conducted in order to assess whether there are significant differences between treatment arms. A sensitivity analysis including these costs will be conducted if differences are non-negligible. Similar analyses will be conducted for capability-adjusted life years from the ICECAP-O.

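### Multiple imputation is named only for the 6-month endpoint and 12 months is a separate model, so on the plain reading observed 6-month GAD-7 scores do not inform the 12-month effect, which is biased if later loss depends on them differently by arm

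*Protocol article*

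**What the plan says.** All references are to the protocol article.

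- **Outcomes:** GAD-7 is collected at baseline, "6 months post-randomisation (the primary endpoint), and 12 months post-randomisation". The primary endpoint is therefore 6 months, and 12 months is a separate time point.
- **Statistical methods, models:** "Separate analyses will be conducted at 6-months (primary analysis timepoint) and 12-months follow-up". The model has "fixed effect covariates (treatment arm and baseline score) and a random effect covariate (therapist"). The 6-month score is not listed as a covariate at 12 months.
- **Statistical methods, missing data:** "It is expected that there will be missing outcome data for some participants". Multiple imputation with Rubin's rules "will be implemented for the primary endpoint". No method is named for missing 12-month GAD-7. An earlier sentence says that secondary outcomes are handled much as the primary one is, without mentioning imputation.
- **Economic evaluation:** "Appropriate multiple imputation techniques will be implemented where data on the EQ-5D-5L or resource use are missing". Clinical effectiveness data will also be used to look for "evidence of continued benefit from the treatment at 12 months and any evidence of a waning of effect", which decides whether the economic model is extended past 12 months.

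**The concern.** Three choices act together: imputation tied to the 6-month endpoint, a separate 12-month model, and covariates limited to arm, baseline score and therapist. A single-time-point mixed model has no repeated measures through which an earlier follow-up score could contribute. Followed as written, a person seen at 6 months and lost by 12 adds nothing to the 12-month estimate, although the 6-month GAD-7 is probably the best available predictor of the missing value.

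Such an analysis assumes that, given arm and baseline, loss after 6 months is unrelated to how the person was doing at 6 months, or at least that any relation is alike in both arms. Participants know their allocation, so people not helped by ACT and people improving on usual care could leave at different rates. The document does not show that they will.

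Waning is a comparison of the 6- and 12-month effects. If one is imputed and the other is not, part of an apparent change could reflect who was lost.

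**Working it through.** **Plan's own figures.** The document gives no 12-month attrition and no correlation with 12-month scores, so there is no 12-month figure to reproduce. The sample size of 296 concerns 6 months. It reproduces to within 3% (288 to 289 in total; power 0.90 to 0.91 at 148 per arm) and is not in question.

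**Inputs from Sample size.** Effect 0.37 SD; correlation 0.55 between 0 and 6 months; 20% attrition at 6 months; 148 per arm; SD about 5 GAD-7 points (2 units = 0.4 SD, and 2/0.4 = 5).

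**Assumptions not in the document.** True effect -0.37 SD at both follow-ups; correlation 0.50 (0-12 months) and 0.70 (6-12 months); later loss of 5% or 15%; log-odds of loss changing by 0.7 per SD of the 6-month score (odds ratio about 2); no therapist clustering.

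**Hand approximation.** If loss in one arm follows the 6-month score with slope *b* and overall probability *p*, the baseline-adjusted 12-month mean among those retained shifts by about

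*b* × *p* × (r[6,12] − r[0,6] × r[0,12])

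The bracket is 0.70 − 0.55 × 0.50 = 0.425.

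- 5% loss: 0.7 × 0.05 × 0.425 = 0.015 SD for one arm; 0.030 for opposite directions.
- 15% loss: 0.7 × 0.15 × 0.425 = 0.045 SD for one arm; 0.089 for opposite directions.
- Same slope in both arms: the two shifts cancel.

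**Simulation** (1.5 million per arm). The 12-month score is regressed on arm and baseline among those observed:

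| Loss after 6 months depends on the 6-month score | Bias at 5% loss | Bias at 15% loss |
|---|---|---|
| Same way in both arms | +0.001 | +0.001 |
| UC only, high scorers leave | +0.013 | +0.042 |
| ACT only, high scorers leave | -0.014 | -0.041 |
| ACT high, UC low scorers leave | -0.030 | -0.086 |
| ACT low, UC high scorers leave | +0.031 | +0.086 |

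A negative bias exaggerates the benefit. At an SD of 5, 0.042 is 0.21 points and 0.086 is 0.43 points.

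**Against sampling error.** With 20% lost at 6 months and 15% of the rest lost later, 148 × 0.80 × 0.85 = 100.6 per arm remain. The SE is about √(2 × (1 − 0.50²)/100.6) = 0.122 SD. A bias of 0.042 is 0.34 SE, and a nominal 95% interval then covers about 94%. A bias of 0.086 is 0.70 SE, with coverage of about 89%.

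**Other assumptions.** With a 6-12 month correlation of 0.65, 20% missing at random at 6 months and 12.5% later loss, an odds ratio of 2 gives 0.03 SD (one arm) or about 0.065 SD (opposite directions). With opposite directions, varying that correlation from 0.5 to 0.8 gives 0.035 to 0.087. The harshest case tried (odds ratio 3, opposite directions, 20% later loss) gives 0.145.

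**Does the 6-month score repair it?** When loss depends on the 6-month score, imputing by arm from the 0- and 6-month scores returns -0.368 to -0.371. When loss depends on the unseen 12-month score (same slopes, 15% loss), imputation only reduces the bias: from 0.077 to 0.052 (UC only) and from 0.150 to 0.099 in absolute size (ACT high, UC low). It removes about a third.

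**The case against.** The strongest reply is that this is SAP content. The article defers to an SAP approved by the Trial Steering Committee. It does not say that imputation is only for 6 months, and treating secondary outcomes in the primary's manner could carry imputation over. Separate models by time point are common and permissible. The bias needs arm-specific dependence that nobody has shown, and it leaves the primary result, sample size and type I error untouched.

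Much of this stands. A reader might infer that the plan commits to dropping everyone without a 12-month score, or that the 12-month clinical and economic results must rest on different people. The text says neither, and both depend on the plain reading. Nor does the economic section set a threshold on the 12-month GAD-7 coefficient. It describes a judgement, and any extrapolation comes with sensitivity analyses.

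What does not stand is that the point is mere omission. The article itself fixes the time point for imputation, the separate models and the covariates. The missing-data paragraph follows the sentence on secondary outcomes and names the primary endpoint alone. Even if imputation were carried over, nothing says that the 6-month score would enter it, and imputing from arm and baseline alone would not remove this bias.

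**Conclusion.** The point holds in a conditional form. On the plain reading, observed 6-month scores do not inform the 12-month GAD-7 effect. That wastes information, and it biases the effect, in either direction, if loss after 6 months depends on the 6-month score differently by arm. Under the assumed values the bias runs from about 0 (equal dependence), through 0.01 to 0.03 SD (5% later loss), to 0.04 to 0.09 SD (15% later loss). The correlations with the 12-month score, the loss rates and the slopes are all assumptions.

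Two stronger readings are not supported. One is that the 12-month effect will be materially wrong: the largest tabulated bias, 0.086/0.37 = 23% of the effect, needs opposite dependence in the two arms and 15% later loss. The other is that joint imputation cures the problem whatever the cause of loss: it does so only where loss depends on observed scores. The 6-month primary result is unaffected. The change is worth making before the SAP is approved because it is cheap and the 12-month effect feeds the judgement on waning.

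**What to change.** In Statistical methods, and in the SAP, extend the missing-data method to 12 months. Impute 6- and 12-month GAD-7 together, separately by arm, with the 0-, 6- and 12-month scores all in the imputation model and therapist clustering respected in the ACT arm. Analyse both time points from the same imputed datasets. One joint 6- and 12-month mixed model, with therapist clustering kept, is an acceptable alternative. Do the same for the secondary outcomes measured repeatedly. Keep the complete-case 12-month result as a sensitivity analysis. If the authors already intend imputation at 12 months, the sentence should say so and state that the 6-month score is used.

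The cost is SAP wording and a little more analysis work, somewhat more if the imputation model carries therapist clustering. No new data are needed. The report should acknowledge that loss driven by the unseen 12-month score would be corrected only in part.
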